### Concomitant care permitted or prohibited during the trial {15d}

Patients are excluded from the study if they receive other current psychotherapeutic or psycho-oncological treatment according to our TAU definition.

### Ancillary and post-trial care {34}

If participants need psychological or psychosocial support after the intervention has ended, they may contact the treatment facility or study staff at any time post-intervention.

### Outcomes {16}

#### Outcomes and measurements

Patient assessment is conducted via a 1-h telephone or face-to-face interview (diagnostic interview, semi-structured interview) and via a standardized self-report questionnaire. Completion of one self-report questionnaire takes approximately 30 to 40 min. Table S1 shows a complete list of outcome measures and other assessments. All self-report questionnaires specified below assess patient-reported outcomes for patients in both groups, ORPHYS and TAU. The assessment battery was found feasible and acceptable in the pilot study.

##### Primary outcome

We assess demoralization using the Demoralization Scale-II (DS-II), a 16-item self-report questionnaire measuring feelings of hopelessness and helplessness as well as loss of meaning and purpose [37, 43]. Items are scored on a 3-point Likert-scale from 0 (never) to 2 (often), with a total score ranging from 0 to 32 (Cronbach’s alpha = 0.93) [44]. Higher scores indicate higher demoralization.

##### Secondary outcomes

We assess the presence of affective and anxiety disorders using the Structured Clinical Interview for the Diagnostic and Statistical Manual of Mental Disorders (DSM-5) [45]. We assess the presence of an adjustment disorder according to the International Classification of Diseases-11 (ICD-11) using the Adjustment Disorder Module of the Composite International Diagnostic Interview (CIDI) [46].

We assess death anxiety using the Death and Dying Distress Scale (DADDS), a 15-item self-report questionnaire measuring concerns related to death and dying in patients with advanced cancer [5, 47]. Items are scored on a 6-point Likert-scale from 0 (no distress) to 5 (extreme distress), with a total score ranging from 0 to 75 (Cronbach’s alpha = 0.91). Higher scores indicate higher levels of death anxiety.

We assess dignity-related distress using two self-report measures: the 7-point Sense of Dignity Item (SDI) ranging from 0 (no sense of loss of dignity) to 6 (extreme sense of loss of dignity) [48] and six items from the Patient Dignity Inventory (PDI) [49] assessing physical symptom distress, body image concerns, and loss of autonomy. PDI items are scored on a 5-point Likert-scale from 0 (no problem) to 5 (an overwhelming problem) (Cronbach’s alpha = 0.91) [50]. Higher scores indicate a higher sense of loss of dignity.

We assess quality of life using the subscales Preparation for the end of life and Life completion of the self-report questionnaire Quality of Life at the End of Life-Cancer-Psychosocial (QUAL-EC-P, [51, 52]). The 9 items are scored on a 5-point Likert scale from 0 (not at all) to 4 (completely), with a total score ranging from 0 to 36 (Cronbach’s alpha = 0.77), and subscale scores ranging from 0 to 16 (Preparation for the end of life) and 0 to 20 (Life completion). Higher scores indicate higher quality of life.

##### Exploratory outcomes

We assess prognostic awareness and perception of end-of-life discussions with health care providers using a semi-structured interview based on the study by El-Jawahri [53]. For prognostic awareness, patients are asked about their perceived goals of the cancer treatment as well as what they perceive to be their oncologists’ goals for their treatment. Patients’ answers will be assigned to one or more categories (e.g., cure, life-prolongation, maintaining quality of life, tumor stabilization) [54]. For end-of-life discussions, patients are asked about whether they discussed their wishes regarding medical treatment (e.g., at the end of life) with their oncologist and how they experienced these conversations.

We assess the perceived relationship with health care providers using the corresponding subscale of the QUAL-EC-P [51, 52]. The 5 items are scored on a 5-point Likert-scale from 0 (not at all) to 4 (completely), with a subscale score ranging from 0 to 20 (Cronbach’s alpha = 0.81). Higher scores indicate a stronger subjective relationship with health care providers.

We assess individual adaptation at the end of life by a variety of psychological constructs, which are measured using reliable and valid self-report questionnaires: end-of-life adaptation (Revised Loss Orientation and Life Engagement in Advanced Cancer Scale, LOLES) [31], depression (Patient Health Questionnaire-9, PHQ-9) [55], anxiety (Generalized Anxiety Disorder Questionnaire-7, GAD-7) [56], desire for hastened death (Schedule of Attitudes Toward Hastened Death–Short Form, SAHD-A) [57], suicidal ideation (Beck Scale for Suicide Ideation, BSS) [58]. Detailed descriptions of the self-report questionnaires can be found in a previous publication [59].

We assess medical interventions near the end of life by reviewing patients’ medical charts. Assessment includes start of last systemic anticancer therapy (chemotherapy, immunotherapy, targeted therapy, hormonal therapy); date of last systemic anticancer therapy (chemotherapy, immunotherapy, targeted therapy, hormonal therapy); emergency room visits in the last 30 days of life, intensive care unit and inpatient hospitalization in the last 30 days of life, documentation of power of attorney/living will, documentation of do-not-resuscitate/do-not-intubate order, date of first receipt of in- or outpatient palliative care,^2^ and date and place of death [61].

##### Other variables

We assess adverse events using the Inventory for Assessing Negative Effects of Psychotherapy (INEP), a 21-item self-report questionnaire measuring to what extent patients experience intrapersonal and interpersonal changes as well as changes regarding work, stigmatization, and therapeutic misconduct [62]. Patients are also asked to indicate whether they attribute these changes to the therapy itself. Six items are scored on a 7-point scale from − 3 (worsening) to 3 (improvement); fifteen items are scored on a 4-point Likert-scale from 0 (not at all) to 4 (completely). If patients attributed changes to the therapy itself, frequencies, means, and standard deviations of negative (− 3 to 1), no (0), and positive changes (1 to 3) are calculated ((Cronbach’s alpha = 0.86).

We assess structural deficits using the OPD-Structure Questionnaire (OPD-SFK, [63]), a 12-item self-report questionnaire measuring personality functioning based on the Operationalized Psychodynamic Diagnosis (OPD, [64]). Items reflect the subscales self-perception, shaping contact, and key relationship models. They are scored on a 5-point Likert-scale from 0 (not at all) to 4 (completely), with a total score ranging from 0 to 48 (Cronbach’s alpha = 0.89). Higher scores indicate higher impaired personality functioning.

We assess interpersonal difficulties using the Inventory of Interpersonal Problems (IIP-32), a 32-item self-report questionnaire measuring distress due to interpersonal problems on eight subscales [65, 66]. Items are scored on a 5-point Likert-scale from 0 (not) to 4 (very much), with a total score ranging from 0 to 128 and subscale scores each ranging from 0 to 32 (Cronbach’s alpha = 0.86) [66]. Higher total scores indicate higher distress due to interpersonal problems; higher subscale scores indicate specific dysfunctional relational patterns.

We assess emotional dependence on others using an 18-item version [67] of the Depressive Experiences Questionnaire (DEQ), a self-report questionnaire measuring feelings of helplessness, loneliness, and fear of rejection due to disruption in a relationship [68–70]. Items are scored on a 7-point Likert-scale from 1 (strongly disagree) to 7 (strongly agree), with a total score ranging from 18 to 126. Higher scores indicate higher dependence on others to regulate emotional distress (Cronbach’s alpha = 0.74–0.83) [71].

We assess perceived relationship communication using the Couple Communication Scale (CSS), a 10-item self-report questionnaire based on the Couple Checkup Scale [72, 73] measuring communication, conflict resolution and relationship satisfaction in romantic relationships. Items are scored on a 5-point Likert-scale from 1 (strongly disagree) to 5 (strongly agree), with a total score ranging from 10 to 50 ((Cronbach’s alpha = 0.91). Higher scores indicate better communication in relationships.

We assess patients’ perceived competence in coping with cancer using subscales Coping competence and Adaptability of the self-report questionnaire Patient Competence Questionnaire (PCQ) measuring resource-oriented coping [74]. The 7 items are scored on a 6-point Likert-scale from 0 (not at all) to 5 (completely), with a total score ranging from 0 to 35, and subscale scores ranging from 0 to 20 (Coping competence, Cronbach’s alpha = 0.74) and 0 to 15 (Adaptability, Cronbach’s alpha = 0.75). Higher scores indicate higher levels of resource-oriented coping.

We collect sociodemographic characteristics (e.g., age, gender, relationship status, children, socioeconomic status, religion/spirituality) within the standardized self-report questionnaire. We collect patients’ medical information (e.g., tumor diagnosis, oncological treatment) via medical chart review.

We assess physical symptom burden using the Memorial Symptom Assessment Scale (MSAS-SF), a 28-item self-report questionnaire measuring the frequency and the distress of physical symptoms due to cancer or its treatment [75]. Items are scored on a 5-point Likert-scale ranging from 0 (not at all distressed) to 4 (very much distressed). The average symptom score is calculated (Cronbach’s alpha = 0.87). Higher scores indicate higher physical symptom burden.

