#### Treatment dosage

In ORPHYS, patients receive 15 to 31 weekly therapy sessions lasting 50 min. This number of therapy sessions is in line with the German Psychotherapy Standard for short-term psychotherapy and typical short-term psychotherapies [41]. It includes 3 to 7 diagnostic sessions, and additional 12 to 24 psychotherapy sessions, depending on patients’ individual needs and goals. The number of sessions translates into approximately 5 to 11 months of treatment duration, taking into account expectable interruptions due to physical condition, medical procedures, or rehabilitation measures. Sessions may be provided via video or telephone. ORPHYS treatment is considered complete per-protocol (PP), if patients have received at least 15 sessions.

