#### TAU (control group)

In line with our pragmatic study approach, content and frequency of TAU sessions may vary between and within the study sites. Details of TAU treatment will be documented by the study personnel on a standardized form (see section Therapy process outcomes). Patients receive routine psycho-oncological treatment as provided by the study centers. TAU includes supportive psycho-oncological interventions according to the German Psycho-Oncology Guideline. There is no requirement for a minimum number of treatment sessions. The dosage is flexibly adapted to individual cases and often includes one session every 3 to 4 weeks over the course of a year.

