## Assignment of interventions: blinding

### Who will be blinded {24a}

Since this is a psychotherapy study with two active intervention groups, blinding of participants and therapists is not possible. Recruitment interviews and assessments (diagnostic interviews, mailing of self-report questionnaires) are conducted only by trained, clinically experienced research assistants, who have no knowledge of patients’ treatment allocation.

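### The only INEP summary described depends on patients attributing the change to therapy, so INEP figures read by arm would mix harm with willingness to attribute

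*Protocol article*

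**What the plan says.** The protocol article, Outcomes {16}, under Other variables, gives the INEP its role: "We assess adverse events using the Inventory for Assessing Negative Effects of Psychotherapy (INEP), a 21-item self-report questionnaire". Change and attribution are separate answers: "Patients are also asked to indicate whether they attribute these changes to the therapy itself". The summary rule follows: "If patients attributed changes to the therapy itself, frequencies, means, and standard deviations of negative", no and positive changes are calculated. No summary irrespective of attribution is described.

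Four other statements bear on how that summary would be read:

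- Outcomes and measurements: "All self-report questionnaires specified below assess patient-reported outcomes for patients in both groups, ORPHYS and TAU".
- Who will be blinded {24a}: "blinding of participants and therapists is not possible".
- Treatment dosage: "In ORPHYS, patients receive 15 to 31 weekly therapy sessions lasting 50 min".
- TAU (control group): "There is no requirement for a minimum number of treatment sessions", and the dosage "often includes one session every 3 to 4 weeks over the course of a year".

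Harms {17} sets up a second channel. Adverse, serious adverse and unanticipated events are documented after each session in both arms, the likelihood of relation to treatment is recorded as an additional item, and all events are to be reported.

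**The concern.** In a randomised trial, the effect of treatment on worsening is estimated by comparing all worsenings between the arms. The patient's opinion about cause is not needed. Restricting the summary to attributed changes brings in a judgement that comes after randomisation, is made by someone who knows the treatment received, and can depend on how much therapy there was to hold responsible. A patient seen weekly in a conflict-focused therapy and a patient seen every few weeks may answer the attribution question differently after the same worsening. A worsening that reflects too little support is also an unlikely candidate for attribution to therapy.

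The rule is also unclear on its face. It promises a frequency of no change among changes attributed to therapy, but a change that did not occur cannot sensibly be attributed. The denominator is not stated. If it is all respondents, the numerator has been filtered by attribution. If it is the patients who attributed a change, as the means and standard deviations imply, the arms are compared on subsets selected after randomisation.

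At stake is how the INEP table can be interpreted. The primary analysis is not affected.

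**Working it through.** No stated figure in the plan has to be reproduced for this point. The check covers contact by arm and then the effect of the attribution condition.

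**1. Contact by arm.** Inputs: weekly ORPHYS sessions, 15 to 31 in all (Treatment dosage); 30% of sessions cancelled (Plans for assessment and collection of outcomes {25a}); TAU often every 3 to 4 weeks for a year (TAU section).

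- TAU over a year: 52/4 = 13 to 52/3 = 17.3 sessions.
- TAU over 6 months: 26/4 = 6.5 to 26/3 = 8.7 sessions.
- ORPHYS over 6 months: 26 × 0.70 = 18.2 sessions.
- Ratio over 6 months: 18.2/8.7 = 2.1 to 18.2/6.5 = 2.8.

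Contact is thus about two to three times as frequent in ORPHYS over 6 months. The totals of about 13 to 17 and 15 to 31 overlap.

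**2. Effect of the condition.** Let h be the proportion of an arm's respondents who worsen on an item and a the proportion of those who attribute it to therapy. The attributed rate over all respondents is h × a. The ratio between arms is (h₁/h₂) × (a₁/a₂), so under equal harm it reduces to a₁/a₂, the ratio of attribution. The documents give neither h nor a; every value below is an assumption.

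| Worsening, ORPHYS v TAU | Attribution, ORPHYS v TAU | Attributed rate | Ratio | All-changes summary |
|---|---|---|---|---|
| 20% v 20% | 60% v 30% | 12% v 6% | 2.0 | 20% v 20% |
| 20% v 20% | 50% v 40% | 10% v 8% | 1.25 | 20% v 20% |
| 20% v 20% | 50% v 50% | 10% v 10% | 1.0 | 20% v 20% |
| 20% v 20% | 30% v 60% | 6% v 12% | 0.5 | 20% v 20% |
| 15% v 30% | 60% v 30% | 9% v 9% | 1.0 | 15% v 30% |

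Under equal harm the attributed ratio runs from 0.5 to 2.0. In the last row a 15-point difference disappears. Where attribution is equal, the ratio is undistorted.

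**3. Whether the session forms replace the INEP.** They are completed after sessions, so opportunities to record rise with attendance. According to Therapy process outcomes, therapists complete them in ORPHYS and study personnel in TAU. The self-report questionnaires are mailed (Recruitment {20}) and do not depend on attending a session. The two channels are complementary.

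**The case against.** The case on the other side is substantial and limits the point in several ways.

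- **Harms as a whole.** A reader might infer that the trial's harm comparison rests on attribution. It does not. Harms {17} commits to reporting all adverse and serious adverse events in both arms, with relatedness as extra information. This stands, and it confines the point to the INEP.
- **Deterioration in TAU.** A reader might infer that it would go unseen. Patients in both arms complete the DS-II, PHQ-9, GAD-7, a suicidal-ideation scale and the IIP-32, none conditioned on attribution. They are not labelled as harm measures, but they would show worsening. This stands.
- **No planned contrast.** The INEP is listed under Other variables with descriptive statistics, and Statistical methods {27a} gives no between-arm INEP test. This stands. The concern is how a descriptive table by arm would be read.
- **Unattributed changes discarded.** The text does not say so, and the SAP, which is not shown, may add a table. It is fair to say only that the one summary described is conditional. That summary is nevertheless a stated rule and can be judged as written.
- **Scope of the coding.** Grouping into negative, no and positive change fits the six items scored from −3 to 3. No summary is spelled out for the other fifteen. This stands.
- **Purpose of the instrument.** It inventories negative effects of psychotherapy, so an attributed summary is legitimate. It is, but as an addition to the unconditional one.
- **Few or no TAU contacts.** A reader might infer this from the absence of a minimum. The usual dosage and the overlapping totals do not support it, and the abstract mentions at least one session. What differs clearly is frequency.

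**Conclusion.** The point holds for the INEP alone. The only summary described for it is conditioned on a post-randomisation judgement by unblinded patients whose session frequency differs by arm, and its no-change category is ill-defined under that condition. Read by arm, the figures would mix harm with willingness to attribute.

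It would go too far to say that they measure attribution instead of harm: they measure attributed harm, a product of the two. Nor do the documents support a claim that the rule favours either arm. The range of 0.5 to 2.0 under equal harm, and the masking of 15% v 30%, rest wholly on assumed rates. Any distortion requires attribution to differ between arms, which is plausible but not shown. This is a worthwhile, inexpensive correction to a descriptive safety summary.

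**What to change.** In Outcomes {16}, Other variables, make the main INEP summary the number of patients with any negative change, and the negative changes per item, by randomised arm, with all INEP respondents in that arm as denominator and irrespective of attribution. Show therapy-attributed changes beneath it as a labelled descriptive subset.

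The same sentence should define a negative change for both item formats, since the printed negative range runs from −3 to 1 and so overlaps the no-change and positive categories, and no grouping is given for the other fifteen items.

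Both answers are already on the questionnaire, so data collection and patient burden are unchanged. The cost is one more table.

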### Harms {17}

After each ORPHYS and TAU session, occurrence and severity of adverse events (new psychological or physical symptoms, progress of disease, hospital admission, death, suicidal thoughts or attempts, difficulties in relationships or other areas of life); serious adverse events (death, life-threatening event, prolonged or persistent disability or incapacity); and unanticipated events as well as their likelihood of being related to the treatment will be documented on a structured, standardized form [62, 92]. All adverse, serious adverse, and unanticipated events will be reported in trial publications.

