### Data management {26}

We document participants’ personal data (name, contact data), corresponding study IDs, and information relevant to the data collection process (e.g., date of follow-up assessments, return of self-report questionnaires, dropout) in Microsoft Access (LTSC 2021). Throughout the data collection process, participants’ study IDs are used (pseudonymization). After completion of the RCT, the study ID list will be deleted. The Microsoft Access file and the audio recordings of the therapy sessions are stored on encrypted flash drives, which are kept in locked cabinets and backed up once a month. Only senior study personnel have access to the Microsoft Access file and the audio files.

Diagnostic interview sheets and self-report questionnaires are stored in locked cabinets. Research assistants will enter the data of the assessments into IBM SPSS Statistics, Version 29 [97]. The SPSS file is stored on secured servers with regular backup, which can only be accessed by the study personnel. To ensure data quality, 20% of the manually-entered data in Microsoft Access and SPSS will be entered twice and range checks for data values will be performed in SPSS. Inconsistencies will be resolved by checking the original data in the questionnaires.

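### The INEP scoring bands for the six bipolar items overlap at 0 and +1, most likely through a dropped minus sign; a minor correction to make before the SAP is final

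*Protocol article*

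**What the plan says.** Protocol article, Outcomes {16}, under Other variables: "We assess adverse events using the Inventory for Assessing Negative Effects of Psychotherapy (INEP), a 21-item self-report questionnaire". Six items lie on a 7-point scale whose lower anchor is minus three. The text continues "3 (worsening) to 3 (improvement); fifteen items are scored on a 4-point Likert-scale from 0 (not at all) to 4 (completely".

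The scoring rule follows: "If patients attributed changes to the therapy itself, frequencies, means, and standard deviations of negative", then an opening bracket and a minus sign, then "3 to 1), no (0), and positive changes (1 to 3) are calculated". No other section restates or corrects these bands.

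Two other sections bear on the point. Data management {26} provides for double entry of 20% of the manually entered data and says that "range checks for data values will be performed in SPSS". Harms {17} commits that "All adverse, serious adverse, and unanticipated events will be reported in trial publications".

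**The concern.** The sentence is an operative rule: it turns answers on a harm instrument into reported results. The introduction to the outcomes section says that the self-report questionnaires cover both arms, so the INEP gives the patients' own account of negative effects, with their own attribution to therapy, in ORPHYS and in TAU.

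Three bands meant to separate negative, no and positive change should place each score in exactly one band. As printed they do not. An analyst or programmer who copied the limits into code would classify a patient who reports no change, or one step of improvement, as having a negative effect of therapy. The three frequencies would sum to more than 100%, and the mean of the negative changes could come out above zero.

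The next instruction for the same instrument has a smaller slip. The other "fifteen items are scored on a 4-point Likert-scale from 0 (not at all) to 4 (completely"), and 0 to 4 is five values, not four.

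**Working it through.** **Inputs.** All come from the INEP paragraph under Other variables: the scale of the six bipolar items (integers −3 to 3), the three printed bands, the attribution condition, and the item counts. The protocol states no harm rate, so there is no figure to reproduce. Its counts are consistent: −3 to 3 gives 7 points, and 6 + 15 = 21 items.

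**Step 1: do the bands form a partition?**

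| Band | As printed | Scores | With the negative band ending at −1 | Scores |
|---|---|---|---|---|
| Negative | −3, −2, −1, 0, 1 | 5 | −3, −2, −1 | 3 |
| None | 0 | 1 | 0 | 1 |
| Positive | 1, 2, 3 | 3 | 1, 2, 3 | 3 |
| Total assignments | | 9 | | 7 |

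As printed, 9 assignments cover 7 scores, and 0 and +1 each fall in two bands. With the upper limit at −1, each score falls in exactly one.

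**Step 2: what would literal use do?** The protocol gives no response distribution, so the three below are assumptions that show the mechanism only. Probabilities are listed for −3, −2, −1, 0, 1, 2, 3.

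- A: 1/7 each.
- B: 0.02, 0.03, 0.05, 0.30, 0.25, 0.20, 0.15.
- C: 0.01, 0.02, 0.05, 0.60, 0.17, 0.10, 0.05.

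Negative share as printed = P(−3) + P(−2) + P(−1) + P(0) + P(1). Negative share as evidently meant = P(−3) + P(−2) + P(−1). For B these are 0.02 + 0.03 + 0.05 + 0.30 + 0.25 = 0.65 and 0.10.

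The rule applies only to changes attributed to therapy, and a patient who scores 0 has no change to attribute. The last two columns therefore drop the zeros and divide by 1 − P(0). For B: (0.10 + 0.25)/0.70 = 50% against 0.10/0.70 = 14.3%.

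| Assumed distribution | Negative, as printed | Negative, ending at −1 | Sum of the three printed bands | As printed, zeros dropped | Ending at −1, zeros dropped |
|---|---|---|---|---|---|
| A | 71.4% | 42.9% | 128.6% | 66.7% | 50% |
| B | 65% | 10% | 155% | 50% | 14.3% |
| C | 85% | 8% | 177% | 62.5% | 20% |

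The mean of the scores called negative, zeros included, is −1.0 as printed against −2.0 under A, +0.12 against −1.70 under B, and +0.06 against −1.50 under C. A positive mean for negative changes shows that the printed limits cannot be the intended ones.

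**Step 3: the fifteen other items.** Integers 0 to 4 are five codes; a 4-point item has four. The text fits a four-code form (0 to 3, or 1 to 4) with a misprinted anchor, or a five-code form with a misprinted number of points. If a four-code form were checked against 0 to 4, one impossible code would pass. If a five-code form were checked as four codes, a valid answer would be flagged. The secondary outcomes text has the same kind of slip for the Patient Dignity Inventory items (5-point, 0 to 5), so the printed anchors cannot be assumed to be the reliable part.

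**The case against.** The strongest reply is that the sentence corrects itself. It gives 0 to no change and 1 to 3 to positive change, on a scale anchored at worsening and improvement, so only −3 to −1 is left for negative change. This is a proofreading slip rather than an analysis choice, and a careful analyst would read it correctly. That stands. The sign might also have been lost when the text was taken from the PDF. This cannot be fully excluded, but it is unlikely, because the minus sign before the 3 survives both in the scale description and in the band itself.

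A reader might infer three stronger things that the document does not support:

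- **That the self-reported harm rate is wrong.** No rate has been calculated, and the rule contradicts itself rather than fixing one wrong rate. Any inflated percentage rests on an assumed distribution and on an analyst coding +1 as negative against the same sentence.
- **That the harm comparison between the arms could not be interpreted.** The bands can apply to only six of the 21 items. The INEP is listed under Other variables and summarised by frequencies, means and standard deviations; the statistical methods section states no between-arm model for it. Adverse and serious adverse events and their relatedness are documented after each session in both arms (Harms {17}) without use of these bands.
- **That the range check cannot be set.** The text gives the endpoints 0 and 4, so a check can be set. Its correct limits are only ambiguous.

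What remains is that the protocol states a scoring rule for a harm measure and states it wrongly. This is not a detail left to the SAP, and an SAP that copied the sentence would copy the error.

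**Conclusion.** The point holds as a minor error. The printed negative band covers 5 of the 7 scores instead of 3, and 2 of the 7 (0 and +1) are assigned twice. Literal use would count no change and slight improvement as therapy-attributed harm. The likely cause is a dropped minus sign, and the intended reading is hardly in doubt.

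The reach is narrow: the descriptive INEP summary of six items. The primary outcome, power, the confirmatory contrast at 6 months and the session-level adverse event records are untouched. The percentages in the working are illustrations under assumed distributions, not estimates for this trial. They shrink when zeros drop out under the attribution condition, although the distortion from +1 remains.

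The mismatch between 4-point and 0 to 4 is a separate wording slip. It leaves the range-check limits for fifteen items unclear and does not add weight to the band error.

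**What to change.** State the bands for the six bipolar items as negative (−3 to −1), none (0) and positive (1 to 3), and say that they apply to those six items only. For the other fifteen, check the printed form, state one coding with matching anchors and number of points, and use it as the limit in the SPSS range check.

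Make both changes before the SAP is finalised. The protocol places its submission before data lock and expects recruitment to run to December 2027, so the cut-off can be settled before the harm data are summarised. The cost is a sentence or two in the protocol and SAP, with no change to data collection, provided the form in use is coded consistently.
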